### Statistical analysis and randomization

The sample size for the feasibility study is to be at least 60 women. For this study, the sample size was not determined based on statistical assumptions and tests, but on practical grounds that each center should recruit 20 participants. Primary and secondary endpoints will be analyzed descriptively. The primary endpoint will be determined according to the criteria shown in Table 4. Secondary endpoints will be described using absolute or relative frequencies, means with standard deviations, or medians with inter-quartile ranges as appropriate, for each of the study arms at the different time points. Measurements at months 3, 6, and 12 will be compared and tested against the baseline values using either parametric or non-parametric tests as appropriate. Randomization is to take place using envelopes, which will be deposited at the study center before the study begins. The group allocation (randomization) will be done centrally, using randomly permuted blocks of length 2–6. The randomization ratio is to be 1:1. We will use participating center and previous breast cancer as stratification factors. Each center will receive consecutively numbered, opaque envelopes, unique to them, split into two sets (one for previously diseased and one for healthy participants), containing the results. For each new participant, the principal investigator in the center will choose and open the first envelope from the diseased or healthy batch accordingly. As the study is not blinded, the allocation result will be concealed neither from participants nor from the principle investigators.

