**Methods:**

Therefore, we intend to enroll 60 BRCA1/2 mutation carriers in a pilot feasibility study (Lifestyle Intervention Study in Women with Hereditary Breast and Ovarian Cancer (LIBRE) pilot). This multi-center, prospective, controlled trial aims to randomize (1:1) participants into a (1) multi-factorial lifestyle intervention group (IG) versus (2) the control group with usual care (CG). The primary endpoint is feasibility and acceptance of a structured interdisciplinary lifestyle intervention program over 12 months (at least 70% of the patients to complete the 1-year intervention). Furthermore, the effects on physical fitness, BMI, quality of life, and stress coping capacity will be investigated.

During the first 3 months, women in the IG will receive structured, individualized and mainly supervised endurance training of ≥18 MET*h/week (MET = metabolic equivalent task) and personal nutritional counseling based on the Mediterranean diet. During the subsequent 9 months, the IG will receive monthly group training sessions and regular telephone contacts for motivation, whereas the CG will only receive usual care (one general counseling on healthy nutrition and benefits of regular physical activity on health status). At randomization and subsequent time points (3, 6, 12 months), cardiopulmonary fitness will be assessed by spiroergometry and nutritional and psychological status by validated questionnaires.

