## Methods

### Trial design

LIBRE-1 will be a multicenter, prospective, two-armed randomized (1:1) controlled clinical trial including *n* = 60 BRCA1 or 2 carriers. The aim of the study is to evaluate adherence to and acceptance of a structured, 1-year exercise program combined with a Mediterranean dietary pattern in BRCA mutation carriers. Additionally, physical fitness, body weight, quality of life, and stress coping capacity will be assessed. The study design is outlined in Fig. 1 and includes four visits (study entry (SE), start of intervention (V0), 3 months after start of intervention (V1), and 12 months after start of intervention (V2)). The schedule of enrollment, interventions, and assessments is shown in Table 1.

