### Study endpoints

The primary endpoint of the study is the number of randomized women who successfully complete the first 3 months of the intervention program and the monitoring/maintenance phase after 1 year. The study is considered feasible if at least 70% of the patients fulfill the criteria (see Table 4 for details).

**Table 4 Tab4:** Criteria for successful completion

Attendance of 70% of the planned lifestyle intervention events (training sessions and nutrition courses) within the first 3 months • Conduct of study visit after 1 year • No withdrawal of informed consent within 1 year • No new occurrence of any of the exclusion criteria during the first 3 months	

Secondary endpoints of the study include the measurements of quality of life (EORTC QLQ-C30-/BR23), stress coping (SSCS), optimism grade (LOT-R), body mass index (BMI), eating habits, nutrient and fat calorie intake (EPIC-FFQ), adherence to a Mediterranean diet (MEDAS), maximal oxygen intake (VO_2_ max), and physical activity (IPAQ). These measurements will be performed after 3, 6, and 12 months of intervention and compared to the baseline measurements at SE.

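### The only tests specified for the secondary endpoints are against baseline; with no between-arm comparison stated, they cannot isolate an intervention effect

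*Protocol article*

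**What the plan says.** The Trial design section describes the study in these terms: "LIBRE-1 will be a multicenter, prospective, two-armed randomized (1:1) controlled clinical trial". The abstract sets an aim beyond feasibility: "Furthermore, the effects on physical fitness, BMI, quality of life, and stress coping capacity will be investigated".

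The comparison for the secondary endpoints is stated twice. Study endpoints says: "These measurements will be performed after 3, 6, and 12 months of intervention and compared to the baseline measurements at SE". Statistical analysis and randomization says: "Measurements at months 3, 6, and 12 will be compared and tested against the baseline values using either parametric or non-parametric tests as appropriate". The same section states "Primary and secondary endpoints will be analyzed descriptively", and promises summaries of the secondary endpoints by frequencies, means with SDs or medians with quartiles, "as appropriate, for each of the study arms at the different time points".

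No section names a between-arm test, estimate or confidence interval. The article also does not say whether the baseline tests are run within each arm or on both arms pooled; within each arm is the natural reading.

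**The concern.** Randomization makes the two arms comparable with each other. It does not make a woman's later value comparable with her earlier one. A before-after test picks up everything that changes over the year: familiarity with spiroergometry and the questionnaires, season, regression to the mean, and being in a study.

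The protocol itself gives reasons to expect change among controls. Under Control group, they receive an introduction lecture, a brochure and a dietitian-led lesson, and are told that such changes in routine should improve quality of life and stress. The Discussion expects motivated volunteers and some controls who follow the exercise instructions of the intervention arm.

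At stake is what can be said about the effects the abstract promises. The abstract also calls the results the basis for a larger trial. The stated tests supply no between-arm estimate for either purpose.

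This is not a detail left to a statistical analysis plan. The article fixes the comparison, and a between-arm analysis specified elsewhere would not remove the baseline tests.

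**Working it through.** **Inputs from the protocol article.** Three centers; a sample size set "but on practical grounds that each center should recruit 20 participants"; "The randomization ratio is to be 1:1"; eight secondary measures under Study endpoints, counting one per instrument (QLQ-C30/-BR23, SSCS, LOT-R, BMI, EPIC-FFQ, MEDAS, VO2 max, IPAQ); the visit schedule in Table 1.

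**The plan's own figure.** 3 × 20 = 60, so 30 per arm. This reproduces the stated minimum. The article gives no alpha, power, SD or effect size.

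**Assumptions, not in the documents.** Two-sided 5% level, complete data, normally distributed change scores, no true difference between arms, and the same mean change in both arms.

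**Step 1: one within-arm test.** For a common change of d SDs of the change score, power is that of a one-sample t test with noncentrality d√n. With n = 30 and d = 0.3 the noncentrality is 0.3 × √30 = 1.643, the critical t on 29 df is 2.045, and power is 0.355. At d = 0.2 it is 0.185.

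**Step 2: intervention arm significant, control arm not.** The arms are independent, so the probability is p(1 − p) = 0.355 × 0.645 = 0.229, about 23%. The arms disagree in either direction with twice that probability, 46%, but only half of those cases show the pattern that favors the intervention.

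**Step 3: if the arms were pooled.** With n = 60 and d = 0.3 the noncentrality is 0.3 × √60 = 2.324 and power is 0.63. Pooling would make the result still less informative about the intervention.

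**Step 4: sensitivity, by simulation (20,000 runs per row, 30 per arm).** Here the common change is in SDs of the measurement. The SD of change is √(2(1 − r)), where r is the correlation between baseline and follow-up.

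| r | Common change | Intervention arm significant | Intervention only | Between-arm test significant |
|---|---|---|---|---|
| 0.5 | 0 | 5% | 5% | 5% |
| 0.5 | 0.2 | 19% | 16% | 5% |
| 0.5 | 0.3 | 36% | 23% | 5% |
| 0.5 | 0.5 | 76% | 19% | 5% |
| 0.7 | 0.3 | 54% | 25% | 5% |
| 0.8 | 0.3 | 71% | 20% | 5% |
| 0.8 | 0.5 | 99% | 1% | 5% |

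Across all scenarios with a common change, the intervention-only pattern occurs in 1% to 25% of runs. The between-arm test rejects in 4.5% to 5.5% throughout.

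**Step 5: number of tests, following Table 1.** At 3 and 12 months: 8 measures × 2 visits × 2 arms = 32. At 6 months Table 1 schedules IPAQ in both arms (2), MEDAS in the intervention arm only (1) and EPIC-FFQ in the intervention arm only (1); spiroergometry, anthropometry and psychological questionnaires are not scheduled. The total is 36, and 36 × 0.05 = 1.8 expected false positives if nothing changes. Taking Study endpoints literally, with everything at all three times, would give 8 × 3 × 2 = 48, but Table 1 does not support that.

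**Step 6: what 30 per arm gives for a between-arm estimate.** With baseline adjustment the residual SD is √(1 − r²). The 95% half-width is 1.96 × √(1 − r²) × √(2/30), which is 0.44, 0.36 and 0.30 SD for r = 0.5, 0.7 and 0.8. The difference detectable with 80% power, using 1.96 + 0.84, is 0.63, 0.52 and 0.43 SD.

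**The case against.** The strongest reply is that this is a feasibility pilot sized on practical grounds, with its analysis labeled descriptive. The primary endpoint is the completion criterion in Table 4, judged against 70%, and the Discussion ties going ahead with the larger trial to compliance and acceptance. No decision rule uses the baseline tests, and the larger trial is aimed at breast cancer incidence and mortality. All of this stands, and it lowers the severity. It does not make a before-after test informative about an effect, and the section that calls the analysis descriptive goes on to commit to testing.

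A reader might infer three stronger things that the document does not support:

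- **That the control arm is unused.** It is summarized at each time point, and the Discussion uses its activity, fitness and diet data to watch for cross-over. It is missing only as a comparator in the stated tests.
- **That within-arm changes will be reported as intervention effects.** No section says so. The abstract's wording makes it a foreseeable misreading, no more.
- **That no SDs will be available for planning.** SDs by arm are promised where means are reported. What is missing is a stated between-arm estimate; the SD of change is not expressly promised.

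The 0.3 SD common change is also an assumption with no source in the document.

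**Conclusion.** The point holds in limited form. The stated tests for the secondary endpoints compare follow-up with baseline only, and such tests cannot support statements about intervention effects. Under the illustrative assumptions (30 per arm, two-sided 5%, no true arm difference, common change of 0.3 SD of the change score) a within-arm test is significant about 36% of the time, and the intervention arm alone about 23%, against about 5% for a between-arm test. These figures depend on the size of the common change, which is unknown. The count of about 36 tests and 1.8 expected false positives depends on following Table 1 and on one test per instrument. The severity is moderate, because the feasibility endpoint and its 70% criterion are untouched.

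**What to change.** Replace the baseline-testing sentence, and align the matching sentence under Study endpoints, along these lines:

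- For each secondary endpoint, at time points where both arms are measured (V1 and V2; month 6 for IPAQ only), report the difference between intervention and control. Adjust it for the baseline value and the stratification factors (center and previous breast cancer), analyze by randomized arm, give a 95% confidence interval and label it exploratory. ANCOVA is one suitable method.
- Use the SE value as baseline, or the first available value for IPAQ.
- Report within-arm changes descriptively, without p-values.

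Two schedule conflicts must be reconciled first:

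- **Psychological questionnaires in controls at V1.** Table 1 schedules them in both arms at 3 months; the Control group section lists SE, V0 and V2 only. If controls are not measured at V1, the comparison is possible only at V2.
- **IPAQ baseline.** Table 1, the physical activity text and the Control group section start it at V0; the IPAQ section starts it at SE. Table 1 places randomization at SE and the trial is open, so a V0 value would be self-reported after allocation is known, and the report should say so.

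The cost is a change of analysis wording plus that reconciliation. The sample size stays at 60. The downside is wide intervals, roughly ±0.3 to ±0.44 SD on the assumptions above, and fewer nominally significant p-values.

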## Discussion

To the best of our knowledge, the LIBRE-1 study is the first prospective randomized lifestyle intervention trial in BRCA mutation carriers worldwide. Since the patients in the intervention arm will be given a strict and intensely structured intervention program, the purpose first is to assess the feasibility of the study design in a multicenter setting including 60 female mutation carriers. We are aware that the study protocol is time-consuming and demanding for the patients including regular exercise and changes in nutritional habits but believe it necessary to cover/investigate all relevant factors. Especially, during the first study visit, the questionnaires amount to a large contribution for the participants. However, the questionnaires can be answered during the waiting time between the examinations, e.g., spiroergometry, ECG, and body composition, lasting approximately half a day. In order to meet a high compliance rate, all participants will be informed beforehand about the time necessary for study examinations. For the time spent for examinations, patients will also receive a small financial reimbursement.

The Mediterranean diet though is widely accepted as a healthy diet in Germany. In addition, randomized controlled intervention studies have revealed that it is effective in the primary prevention of cardiovascular diseases [45], in improving diabetes [46] and cognitive function [47], and recently also in the primary prevention of invasive breast cancer [48].

Once compliance and acceptance of the study protocol have been proven (LIBRE-1), we will proceed with a larger cohort of mutation carriers with the intention to investigate whether the improvement of physical fitness, body weight, quality of life, and stress coping capacity leads to a reduction of breast cancer risk, progression of disease, and even mortality. On the basis of the LIBRE-1 results, it will be possible to outline a lifestyle program with high adherence even over 12 months of intervention (LIBRE trial). The current feasibility study will also reveal barriers to and constraints of the intervention, which will then have to be modified for the larger clinical trial.

One of the foreseen limitations of the trial will be selection bias for those patients being interested in lifestyle intervention and for those who will be randomized to usual care, especially for highly motivated participants. The latter patients may be disappointed on being assigned to the control arm and might either withdraw from the study or follow exercise instructions from the IG. These biases cannot be excluded in any lifestyle intervention trial. However, physical activity will be assessed using questionnaires and an accelerometer in both arms, and any cross-over of patients can be monitored. In addition, physical fitness will be objectively assessed by spiroergometry in both arms, which will also yield information on the long-term involvement of physical activity.

On the other hand, restraints for less motivated patients, e.g., due to professional obligations or as cares for children or other family members, may have an impact on adherence to supervised exercise sessions and everyday physical activities. In addition, a cross-over from CG to IG group for the Mediterranean dietary pattern cannot be excluded as previously outlined for physical activity. However, nutritional habits will also be assessed by questionnaire and BMI and body composition measured in both groups. Because of these problems in lifestyle intervention trials, it is a clear aim to avoid cross-over or bias of investigations by assuring that patients be treated identically regardless of the group assignment.

This LIBRE initiative (pilot and clinical study) will have the potential to reveal whether a structured lifestyle intervention program may prevent tumor incidence in BRCA mutation carriers. This will have to be compared with current risk-reducing strategies for women at risk, including prophylactic mastectomy, and could then be added to early detection programs. Furthermore, by following a structured exercise program and dietary changes, mutation carriers will attain an independent and self-governed role in cancer prevention and successfully reduce their stress levels [39]. By improving and optimizing the latter, we expect a preventive health effect not only on a somatic but also on the mental status of these patients.

## Abbreviations

BIA: Bioelectric impedance analysis
BMI: Body mass index
BRCA: Breast cancer gene
CHC: Coronary heart condition
COPD: Chronic obstructive pulmonary disease
ECG: Electrocardiogram
GC-HBOC: German Consortium Hereditary Breast Ovarian Cancer
HBT: Home-based training
IPAQ: International Physical Activity Questionnaire
LIBRE: Lifestyle Intervention Study in Women with Hereditary Breast and Ovarian Cancer
LOT-R: Life of Orientation Test-Revised
MD: Mediterranean dietary pattern
MET: Metabolic equivalent task
QLQ-C30/-BR23: Quality of Life Questionnaire Core 30 and Breast Cancer Module 23
SE: Study entry
SSCS: Screening Scale for Chronic Stress
V: Visit
